### Eligibility criteria

Patients will be recruited through their primary contact in the clinics. The project manager (PhD student and psychiatric nurse ([name])) and three research assistants (two psychiatric nurses and a medical student) will perform the interventions.

#### Inclusion criteria

Participants: Patients with first depressive episode or with recurrent depressive disorders according to ICD-10 (F32–33) or F32–33 in combination with anxiety disorders F40–41.2 (males and females, aged ≥ 18 years) who receive outpatient treatment in The Mood Disorders Clinic, Aarhus University Hospital Psychiatry, Denmark, and in the Mental Health Department Odense – University Clinic, Mental Health Service, Region of Southern Denmark.Participants must
Experience poor sleep and have a Global Pittsburgh Sleep Quality Index Score ≥ 5 [3, 5, 14].Report one or more of the following:
Sleep onset latency ≥ 31 min, occurring ≥ 3 nights a week, for ≥ 14 days, [14, 23]Wake time after sleep onset of ≥ 31 min occurring ≥ 3 nights a week for ≥ 14 days, [14, 23]Early morning awakenings ≥ 3 nights a week for ≥ 14 days [14, 23].

In this trial, early morning awakening is defined as the final morning awakening with a wake-up time ≥ 1 h prior to desired wake up time [14, 24, 25].

#### Exclusion criteria

Patients that, according to ICD-10 criteria, have been depressed > 2 yearsPatients suffering from hypersomnia (ICD-10: F51.13)Patients with harmful use of or dependence on psychoactive drugs (ICD-10: F10–19)Patients with diseases directly influencing sleep quality (such as severe chronic pain issues, sleep apnoea)Patients who report breathing issues during the eligibility PSQI interviewPatients with Circadian Rhythm Sleep-Wake Disorders (ICD-10; G47.20–47.26)Participation in other research interventions during the intervention period.

### Intervention

The intervention is the 7-kg Protac Ball Blanket™ Flexible cotton 200 cm filled with loose quit plastic balls. The blanket is characterized by the movement of the plastic balls, which provides a changing sensory stimulation. For more information, see www.protac.dk.

Treatment as usual in this trial refers to the regular duvet each patient usually uses when sleeping at home. Information (e.g. size, weight, material) on each of the patient’s duvets will be registered before inclusion for the purpose of describing the average duvets used as control blanket in this trial.

#### Actigraphy

Actigraphy will be used as an instrument to objectively evaluate sleep in this trial.

The devise used is a Motionlogger Micro Watch (Version 1.99.5.1.) from Ambulatory Monitoring Inc. New York, USA. It is a portable device that is the size of a large wristwatch. The actigraph is an accelerometer that detects the intensity and the amount of movements as a function of time [26]. Movements are monitored continuously and stored within the device. Subsequent analysis of frequency and patterns of movement by means of validated algorithms permits detection of sleep-wake patterns. For this trial, movements will be sampled in 1-min epochs. The data activity collection modes are Zero Crossing (ZC) and Proportional Integrating Measure (PIM) [26, 27]. All movements that are scored above a preset threshold using the algorithm Cole-Kripke scoring algorithm are scored as “awake” and those that are below this threshold are scored as “sleep”. The algorithm correctly distinguished sleep from wakefulness 88% of the time when compared to polysomnography [27].

All patients will be asked to wear the actigraph on the wrist of their non-dominant hand for the consecutive 4 weeks (28 nights in total) in their own home environments. As the device is waterproof, patients are instructed to wear the actigraph 24 h a day, including when taking showers. Patients are instructed to press the event-marker as they go to bed, wake up, and when they get out of bed at the start of the next day. These starts and stop intervals will be registered in sleep diaries as patients will be able to visually see if they forgot the registration.

[name] and an experienced sleep scientist will perform the scoring and analysis of actigraphic records. The degree of agreement between raters will be calculated and reported using the Intraclass Correlation Coefficient. Data will be analysed using the MotionLogger Analysis Software program Action-W (AW2) (Version 2.7.2).

The pertinent sleep variables chosen for this trial are total sleep time after sleep onset (in minutes) (TST), sleep onset latency (SOL), number of awakenings, and wake after sleep onset (WASO) (for definitions of variables, see the “Outcomes” section).

#### The practicalities of the trial

Figure 1 outlines the participant timeline, and Fig. 2 shows the standard protocol items recommended by SPIRIT: Schedule for enrolment, intervention, and assessments. Additional file 1 presents The Standard Protocol Items: Recommendations for Interventional Trials (SPIRIT) checklist.

**Fig. 1 Fig1:**
[figure not shown]
Participant timeline

**Fig. 2 Fig2:**
[figure not shown]
Study schedule for enrolment, intervention, and assessments

The participant timeline (Fig. 1) shows patients will meet with data collectors four times in total. Initially for the purpose of recruitment and written consent (visit 1), the second visit (Visit 2) consists of the installation and activation of actigraphs. Baseline data will be gathered using six validated questionnaires (see the “Data collection methods” section for further details). Patients will be introduced to the sleep and medication diary (Table 2) presented as a supplementary material. Data from sleep diaries will be used to aid the process of scoring sleep-wake stages, when analyzing patients’ actigraphic sleep records. Subsequently, patients are randomized into either (1) sequence “AB” or (2) sequence “BA” each lasting 4 weeks. Patients randomized to the AB sequence receive treatment A (Protac Ball Blanket™, Flexible, 7 kg) in the first 2 weeks (14 nights) and switch to treatment B (treatment as usual = regular duvet) in the second period, whereas patients that are randomized to the BA sequence receive treatment B in the first period and treatment A in the second period. This means that participants will serve as their own controls.

In both sequences, patients receive general sleep advice prior to participation [4]. The rationale behind this is to avoid behavioural irregularities between periods in order to make comparison of data possible. Patients are recommended to avoid major variations in their sleep-wake patterns from day to day during the trial. But also to avoid major variations in their sleep environment and nicotine, caffeine, alcohol and food consumption directly before bed. Patients are also advised to limit daytime naps to a maximum of 30 min.

The third visit (visit 3) at day 15 consists of a switch-over visit to either receive the intervention or treatment as usual. All six questionnaires will be repeated. Data concerning sleep and medication will be downloaded from actigraphy and collected from diaries for the first 2-week period (14 days and nights). The procedures will be repeated at the end of the study (week four = day 29) at visit 4.

The investigators allow a + 7-day non-compliance with the scheduled visit dates (2 weeks apart) in case patients experience relapse or become ill, which can hinder a physical meeting. The allocated treatment will be discontinued in all cases of patient requests, hospitalization, and alcohol or drug abuse. Patients may withdraw from the trial for any reason. The investigators may withdraw the patient from the study if the patient is unwilling or unable to wear the actigraph, as the analysis of the primary outcome data depends on these measures.

In case patients experience intolerable adverse events and other unintended effects of trial interventions or trial conduct, the reasons will be recorded in the patient’s Case Report Form (CRF) and securely stored in REDCap. All serious adverse events will be reported to the Danish Scientific Ethics Committee, in the final article, and also to Protac A/S.

The overall protocol adherence is secured by [name] and the three research assistants. Individual training of research assistants is completed before study initiation. In order to secure full data completion, we have registered all questions from questionnaires as “required” in the REDCap (REDCap 8.5.22 2019 Vanderbilt University) system. Hereby, the system will immediately remind us of any missing data when patients are present. REDCap (Research Electronic Data Capture) is a secure browser-based, metadata-driven EDC software solution and workflow methodology for designing clinical and research databases. All data from this trial will be securely stored in REDCap.

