## Abstract

**Background:**

Depression affects approx. 4% of the global population and is often accompanied by insomnia. Medications used to treat insomnia can have side effects such as development of tolerance and addiction. The Protac Ball Blanket™ (PBB) is a non-pharmacological supplement to sedatives and hypnotics, but evidence for the efficacy of PBB is needed before the treatment is implemented. The objective of this trial is to test the efficacy of PBB on insomnia caused by depression in a randomized controlled design.

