## Methods/design

### Objectives

The objective is to investigate the efficacy of PBB on insomnia caused by depression in a randomized controlled design.

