### Data collection methods

The following data will be collected for the purpose of the research and recruitment:
From hospital records: Name, phone number, personal identification number from the Danish Civil Registration System (CPR number), diagnosis, medication prescriptions.From actigraphy (Motionlogger Micro Watch from Ambulatory Monitoring Inc. NY): Total sleep time, sleep onset latency, number of awakenings, wake after sleep onset.From diaries: The use of sleep and anxiety medications, bedtime and time of getting out of bed, number of awakenings and duration, wake after sleep onset and daytime naps including lengths registered in minutes.From six validated questionnaires: The Global PSQI Score using The Pittsburgh Sleep Quality Index (PSQI), the insomnia severity score using the Insomnia Severity Index (ISI), depressive symptoms using the Major Depression Inventory (MDI) and 6-item Hamilton Rating Scale for Depression (HAM-D_6_), patients’ self-reported symptoms using the Self-reported Symptom State Scales (SCL-28) and anxiety symptoms using the Beck Anxiety Index (BAI) [3, 25, 28–30].

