### Data monitoring

No data monitoring committee (DMC) will be established for this trial. Further, no interim analysis will be performed due to the short duration of the trial and a minimal intervention risk.

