In summary, this is a randomized crossover multicentre trial testing the efficacy of Protac Ball Blankets™ on insomnia in depression treated in an outpatient setting. An easy identification of the included patients by clearly defined inclusion criteria, together with the multicentre design, supports the broad clinical relevance of the study results. Because both treatments are evaluated for the same individual, the treatment effect can be estimated based on an average of within-individual differences. Hereby, the crossover design removes between-patient variation and patients can indicate clear preferences for PBB vs regular duvets. The outcome of this trial is of high interest as the PBB may be a potential non-pharmacological supplement to medical treatment of patients with insomnia due to depression.

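### Adverse-event recording rests on an undefined 'intolerable' threshold and only serious events are committed to publication, so non-serious discomfort with the blanket may be under-recorded and unreported

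*Protocol article*

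**What the plan says.** In the protocol article, under 'The practicalities of the trial', directly after the rules on discontinuation and withdrawal, the recording rule reads: "In case patients experience intolerable adverse events and other unintended effects of trial interventions or trial conduct, the reasons will be recorded" in the case report form and kept in REDCap. The next sentence makes the reporting commitment: "All serious adverse events will be reported to the Danish Scientific Ethics Committee, in the final article, and also to Protac A/S". The section 'Data monitoring' states "No data monitoring committee (DMC) will be established for this trial" and adds that "no interim analysis will be performed due to the short duration of the trial and a minimal intervention risk".

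The section 'Data collection methods' opens with "The following data will be collected for the purpose of the research and recruitment" and then names hospital records, actigraphy, diaries and six questionnaires. The stated aim is confined to efficacy: "The objective is to investigate the efficacy of PBB on insomnia caused by depression in a randomized controlled design".

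**The concern.** A recording rule should let two people faced with the same complaint make the same entry. This one does not. A patient who finds the 7-kg blanket hot, heavy or noisy but keeps using it may or may not be entered, depending on how the sentence is read and by whom. Patients and operators are not blinded ('Blinding'), so the judgement is made knowing which blanket is in use.

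At stake is the harms half of the result. The abstract gives drug side effects as background for the trial ("Medications used to treat insomnia can have side effects such as development of tolerance and addiction"), and the discussion presents the blanket as a possible addition to medication ("the PBB may be a potential non-pharmacological supplement to medical treatment of patients with insomnia due to depression"). A reader of the final article will therefore want to know how well the blanket was tolerated. If non-serious complaints are collected haphazardly, a short list of events could reflect the recording rule as much as the blanket. The crossover gives every completing patient a period on each blanket, so a within-patient comparison of complaints is available and would go unused.

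**Working it through.** The point rests on the wording, so the relevant places are set side by side first. A short calculation then shows what complete recording could and could not establish.

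**1. The recording rule.** It has two limbs.
- The first concerns adverse events that are intolerable. No definition or scale is given.
- The second concerns other unintended effects of the interventions or of the conduct of the trial. It states no severity threshold, but it requires a judgement that the trial caused the effect.
- For both limbs, what is recorded is the reasons. Coming straight after the discontinuation rules, this can be read as a note of why a patient stopped rather than as a log of events.

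**2. Whether another stated item fills the gap.**

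| Section | What it lists | Adverse-event or tolerability item |
|---|---|---|
| The practicalities of the trial (visits 3 and 4) | six questionnaires, actigraphy download, sleep and medication diaries | none |
| Outcomes | sleep time, latency, awakenings, wake after onset, sedative use, symptom scales | none |
| Data collection methods | the four sources above, in detail down to nap length | none |

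**3. The publication commitment.** Serious events go into the article. For a non-serious event that led a patient to stop, the text promises a recorded reason but not a published one.

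**4. Link to the analysis.** 'Statistical methods' removes patients whose actigraphy is missing for one period and imputes nothing. A patient who leaves during the blanket period because of non-serious discomfort, without usable actigraphy, is therefore absent from the sleep-time result, and publication of the reason is not promised. (A patient who merely changes blanket but keeps the actigraph stays in.) The plan aims for 45 patients against a required 37, so it allows for 45 − 37 = 8 losses, or 8/45 = 17.8%.

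**5. The sample size is not in question.** With a detectable difference of 20 min and a standard deviation of the difference of 42 min, d = 20/42 = 0.476. A two-sided paired t test at 5% has power 0.793 with n = 36 and 0.805 with n = 37, which reproduces the stated 37.

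**6. What full recording could show (illustration).** If every event were captured and none occurred, the one-sided 95% upper bound on the event rate is 1 − 0.05^(1/n): 6.4% for n = 45 and 7.8% for n = 37. The chance of seeing at least one event with true rate p is 1 − (1 − p)^n:

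| Assumed p | n = 45 | n = 37 |
|---|---|---|
| 2% | 0.60 | 0.53 |
| 5% | 0.90 | 0.85 |
| 10% | 0.99 | 0.98 |

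Complaints of 5% or more would probably surface if everyone were asked. Rare harms would not be excluded even then.

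**The case against.** The strongest reply is that this is a condensed article about an efficacy trial of a non-drug product. How events are elicited, graded and tabulated normally sits in the full protocol, the case report form or the analysis plan. The assessment schedule in Figure 2 and the supplementary diary table are not shown either. This stands as far as silence goes. It does not cover the recording sentence, which is stated and is unclear on its face.

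Second, some deterioration on the blanket would show in the planned data: anxiety, insomnia severity, sleep quality, awakenings and wake time are compared within patients between the two periods. That is true, but these are efficacy measures, and they would not identify discomfort or why someone stopped.

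Third, a reader might infer more than the text supports:
- **That events are recorded only if intolerable.** The second limb has no stated severity threshold and can be read to include tolerable discomfort.
- **That only serious events will be published.** The text promises these and does not bar the others.
- **That the trial claims the blanket is a low-risk supplement to drugs.** No section says so. Minimal risk appears once, as one of two reasons for having no interim analysis, and no safety conclusion is planned.
- **That the exclusions show an expected hazard.** Sleep apnoea and severe chronic pain are excluded as influences on sleep, and no reason is given for excluding breathing issues.

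These limits are accepted, and the point is confined accordingly.

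**Conclusion.** The point holds as a weakness in a stated rule. The threshold word is undefined, the second limb is ambiguous, reasons rather than events are recorded, and the reporting commitment extends only to serious events, with no listed adverse-event item to compensate. Non-serious discomfort with the blanket, including discomfort that ends treatment, may therefore be under-recorded and unpublished, and the premise of minimal risk is not tested by the listed data.

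Its size is modest. The primary outcome, the required 37 patients and the planned test are untouched. How many events would be missed cannot be stated, because the document gives no event rate and the second limb may catch some or all of them. The conclusion assumes that the article's wording is what staff follow. If the full protocol already collects events systematically in both periods and commits to reporting them, only the sentence needs correcting. This is a worthwhile, cheap improvement rather than a threat to the trial's validity.

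**What to change.** In 'The practicalities of the trial', delete the word 'intolerable' from the recording sentence and state that events themselves, not just reasons, are recorded. Then:

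- At visits 3 and 4, ask every patient the same adverse-event question about the period just ended, worded identically for the blanket and the duvet.
- Record every event regardless of severity, with onset date and the blanket in use.
- Commit the final article to counts by period (ball blanket versus duvet) and to reasons for stopping, alongside serious events.
- Add the item to 'Data collection methods'.

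Recruitment began in November 2019, so if the question is introduced part-way, give the number of patients actually asked as the denominator.

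The cost is one short REDCap form and a few minutes at each of two existing visits, with no extra visits or staff. The rules on discontinuing treatment are not affected by this proposal.

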### Outcomes

#### Primary outcome measure

Changes in total night-time sleep (TST) after sleep onset measured by actigraphy [time frame: 4 weeks = 28 days]. The investigators will detect the change in total night-time sleep in minutes (i.e. actual sleep time, excluding sleep latency and wakes after sleep onset) by comparing the means of the difference in total sleep time for each participant between the two periods (A and B). The night-time sleep frame is defined as sleep occurring during a 12-h night interval (21:00 to 08:59 h). The investigators designate the first sleep episode after 2100 h as the first nocturnal sleep episode; if the individual is already asleep at that time, the bedtime will be moved earlier to the first epoch of wake prior to sleep onset [26].

#### Secondary outcome measures

Changes in sleep onset latency (SOL) will be measured by actigraphy [time frame: 28 days]. The investigators will measure patients’ sleep onset latency in minutes (time between registered bedtime in sleep diaries and first sleep onset measured by actigraphy) and compare the means of the difference for each participant between the two periods (A and B).Changes in number of awakenings measured by actigraphy [time frame: 4 weeks = 28 days]. The investigators will measure the number of awakenings between first sleep onset and the last wake up time registry and compare the means of the difference between periods (A and B) for each participant.Changes in wake after sleep onset (WASO) will be measured by actigraphy [time frame: 4 weeks = 28 days]. The investigators will measure patients’ total time awake between initial sleep onset and the final morning awakening (WASO) in minutes and compare the means of the difference between periods for each participant.Daily use of sedatives and hypnotics will be measured by medication registration use in sleep diaries [time frame: 4 weeks = 28 days]. The investigators will measure the change in total use of per need sedatives and hypnotics in mg by comparing the means of the difference for each participant between periods.Quality of sleep measured by questionnaire using the Pittsburgh Sleep Quality Index (PSQI) [time frame: data will be collected at baseline (visit 2), after 2 weeks (visit 3), and after 4 weeks (visit 4)]. The investigators will measure and report the change in quality of sleep between period A and B. For each participant, the difference between the PSQI measured at the first and the last visit (2 weeks apart) of the exposure period will be subtracted from the difference between the PSQI measured at the first and the last visit (2 weeks apart) of the control period. The total Pittsburgh Sleep Quality Index Score between 0 and 21, with “0” indicating no difficulty and “21” indicating severe difficulties, is reported. Because there will be less than 30 days between assessment at visit 3 and visit 4 and the standard PSQI is a retrospective 30-day instrument, we will use a modified version of the PSQI in which the patients will only be asked about their subjective sleep quality during the past 14 days.Symptoms of depression will be measured by the self-reported Hamilton Depression Rating Scale (HAM-D_6_). Data will be collected at baseline, after 2 weeks, and after 4 weeks. The investigators will measure the change in self-reported symptoms of depression between periods. For each patient, the difference between the scores measured at the first and last visit (2 weeks apart) of the exposure sequence will be subtracted from the difference between the scores measured at the first and last visit (2 weeks apart) of the control period. The total sum scores between 0 and 50 will be reported, where higher values represent worse outcome.Insomnia Severity Status will be measured by questionnaire using the Insomnia Severity Index (ISI). Data will be collected at baseline, after 2 weeks, and after 4 weeks. The investigators will measure the change in patients’ insomnia severity status between periods. For each patient, the difference between the scores measured at the first and last visit (2 weeks apart) of the exposure period will be subtracted from the difference between the scores measured at the first and last visit (2 weeks apart) of the control period. The total scores between 0 and 28 will be reported, where higher values represent worse outcomes.Patients self-reported symptoms of depression measured by questionnaire using the Major Depression Inventory (MDI) [time frame: data will be collected at baseline (visit 2), after 2 weeks (visit 3), and after 4 weeks (visit 4)]. The investigators will measure the change in self-reported symptoms of depression between periods. For each patient, the difference between the scores measured at the first and last visit (2 weeks apart) of the exposure period will be subtracted from the difference between the scores measured at the first and last visit (2 weeks apart) of the control period. The total score between 0 and 50 is reported, where higher values represent worse outcomes.Symptoms of anxiety will be measured by questionnaire using the Beck Anxiety Index (BAI). Data will be collected at baseline (visit 2), after 2 weeks (visit 3), and after 4 weeks (visit 4).The investigators will measure the change in self-reported symptoms of anxiety between periods. For each patient, the difference between the scores measured at the first and last visit (2 weeks apart) of the exposure period will be subtracted from the difference between the scores measured at the first and last visit (2 weeks apart) of the control period. The total score between 0 and 63 for each visit is reported, where higher values represent worse outcomes.Patient-reported outcomes concerning interpersonal sensitivity, neurasthenia, anxiety, and depression will be measured by questionnaire using The Self-Reported Symptom State Scale (SCL-28) [time frame: data will be collected at baseline (visit 2), after 2 weeks (visit 3), and after 4 weeks (visit 4)]. The investigators will measure the change in self-reported symptoms between period A and B or B and A. For each patient, the difference between the scores measured at the first and last visit (2 weeks apart) of the exposure period will be subtracted from the difference between the scores measured at the first and last visit (2 weeks apart) of the control period. Sub scales are combined to compute a total score. The range for each sub scale is: Interpersonal Sensitivity 0–32, Neurasthenia 0–28, Anxiety 0–32, and Depression 0–24. Both total score and sub scale scores will be reported. The total score ranges between 0 and 112, where higher value represents worse outcomes. Because of an overlap in one question between the sub scales anxiety and depression question, number 31 is only considered in the total sum scores.

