### Trial design and study setting

This multicentre trial has a randomized 2-sequence, 2-period, 2-treatment crossover design. The rationale for choosing a crossover design is as follows:
Traditionally, the recruitment of depressed patients for research trials is heavily challenged due to the nature of depression, and by choosing a crossover design, we can achieve the same precision as a parallel group trial with a lower sample size [21].We further expect easier recruitment and fewer drop-outs as all patients get to try the PBB intervention compared to a parallel group design.

We are not including a washout period in the trial design for one reason:
The clinical nature and mechanism of the PBB is unlikely to have a residual effect that persists into the subsequent period, as PBBs only cause effect when patients are exposed to the product.

The data collection period lasts 4 weeks (28 nights in total) with planned inclusion of 45 patients. The study protocol adheres to the SPIRIT (Standard Protocol Items: Recommendations for Interventional Trials) reporting guidelines [22].

The trial takes place in two outpatient settings, The Mood Disorders Clinic, Aarhus University Hospital Psychiatry, Central Denmark Region, and in the Mental Health Department Odense – University Clinic, Mental Health Service, Region of Southern Denmark. Both hospitals are public university hospitals. In Denmark, public hospitals containing outpatient clinics are free of charge and treat all patients in need of urgent treatment of depression.

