### Statistical methods

Paired, two-sided analyses will be performed. If the differences in the measures between the exposure and control periods for each patient are normally distributed, as we expect, we will use a Student’s *t* test to test the null hypotheses of no differences. For the non-normal distributions, non-parametric tests, e.g. Wilcoxon signed-rank tests or Fisher’s exact tests will be used.

All data with or without protocol violation will be included in the analysis with complete outcome data for all randomized participants. Because the analyses are based on the differences between period A and B or B and A for each patient, we will perform complete case analysis (i.e. participants with missing actigraphic data from one of the periods will be removed from the analysis). An intention to treat analysis will be performed, i.e. patients that in one or both of the periods use an “incorrect”, non-study blanket will be kept in the analyses in their randomized sequence group. We will not account for missing data by imputation.

The level of statistical significance will be set to 5%.

The randomization will determine whether the participants will begin or end with a PBB. The baseline characteristics of these two groups will be presented in a table. Baseline information on sleep will be based on The Pittsburgh Sleep Quality Index (PSQI) and the Insomnia Severity Index (ISI) and not collected via actigraphy.

There will be no wash-out period in this trial because the PBB are expected to have no residual effect persisting in the subsequent periods. This assumption is based on the biological mechanisms of the ball blanket and on clinical experience, but there are no studies to corroborate this expectation. This aspect of the design, however, is expected to lead to bias toward the null, i.e. that the study will not overestimate a potential effect of PBB. The assumption of no carry-over effect in the data will be ruled out in a preliminary test. The sum of the TST values will be calculated for the time period when using PBB and when using patients’ own duvets for each participant. This will be compared across the sequence groups by means of an independent *t* test. If this test yields a statistically significant result, the usual test for differences between the effects of treatment A or B will not be applied [31].

Data will be analysed using Stata IC15 (Stata Corp, College Station, TX, USA).

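### The change-versus-change contrast for the six questionnaires counts the switch visit twice and, with no residual effect, estimates 1.5 times the true effect

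*Protocol article*

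**What the plan says.** *Secondary outcome measures* defines the PSQI effect in two halves: "the difference between the PSQI measured at the first and the last visit (2 weeks apart) of the exposure period will be subtracted", and this is taken "from the difference between the PSQI measured at the first and the last visit (2 weeks apart) of the control period". The contrast is thus control-period change minus exposure-period change. ISI, MDI, BAI and SCL-28 carry the same rule: "For each patient, the difference between the scores measured at the first and last visit (2 weeks apart) of the exposure period will be subtracted", again with the control-period change as the quantity it is taken from. HAM-D6 has it too, except that it says sequence where the others say period.

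There are three questionnaire time points: "Data will be collected at baseline, after 2 weeks, and after 4 weeks". The visit description under *The practicalities of the trial* fixes the middle one: "The third visit (visit 3) at day 15 consists of a switch-over visit to either receive the intervention or treatment as usual", and all six questionnaires are completed then.

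There is no washout. *Trial design and study setting* justifies this on the ground that "PBBs only cause effect when patients are exposed to the product". *Statistical methods* repeats the assumption of no residual effect, admits that no studies support it, and concludes that "the study will not overestimate a potential effect of PBB".

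The actigraphy and medication outcomes are defined differently: they compare the two periods directly.

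**The concern.** Subtracting a period-specific baseline makes sense in a crossover when each period starts from an untreated value. Here only period 1 does. In sequence AB the starting value of the control period is measured after two weeks on the blanket. If the effect then disappears, as the plan assumes, the score moves back during the control period. The contrast counts that return as further benefit, on top of the gain already counted in the exposure period.

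What is at stake is the size of the reported effect on six scales that readers will judge for clinical relevance. As a hypothetical example, a true 4-point fall in ISI would be reported on average as 1.5 × 4 = 6 points. The trial would also report two different quantities as the effect of the blanket: one for actigraphy and medication, another for the questionnaires.

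**Working it through.** **Inputs.** Y0, Y1 and Y2 are the scores at visits 2, 3 and 4 (*Secondary outcome measures*). Control is the patient's own usual duvet (*Intervention*), so Y0 is a control-condition value. Let τ be the true shift while the blanket is in use and c the fraction that persists after removal. The plan assumes c = 0. The allocation ratio is not stated; 1:1 is assumed.

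**Plan's own figure.** For the primary outcome, a difference of 20 min, an SD of 42 min, two-sided 5% and 80% power give n = 37 by the noncentral t (power 0.805). The stated N = 37 is reproduced. No SD, correlation or power is given for any questionnaire.

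**Form of the contrast.** In AB it is (Y2 − Y1) − (Y1 − Y0) = Y0 − 2·Y1 + Y2. In BA it is (Y1 − Y0) − (Y2 − Y1) = 2·Y1 − Y0 − Y2. Visit 3 has weight 2 in both.

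**Expected size with c = 0.**

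| Sequence | Exposure change | Control change | Magnitude of contrast |
|---|---|---|---|
| AB | τ | −τ | 2τ |
| BA | τ | 0 | τ |

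The balanced mean is (2τ + τ)/2 = 1.5τ. With n_AB of n patients in AB the factor is 1 + n_AB/n: 1.49 to 1.51 for 18/19 splits of 37 or 22/23 splits of 45. In 20,000 simulated trials (18 AB, 19 BA) with τ = 20 the mean was 29.7.

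**Expected size with persistence.** In AB the control change becomes −(1 − c)τ, so the contrast is (2 − c)τ. BA stays at τ. The mean is (3 − c)/2 × τ: 1.5τ at c = 0, 1.25τ at c = 0.5, τ at c = 1.

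**End-of-period comparison.** Blanket score minus duvet score gives (1 − c)τ in AB and τ in BA, mean (1 − c/2)τ. For c between 0 and 1 its magnitude never exceeds that of τ.

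**Type I error.** With τ = 0, any common visit-to-visit shift enters AB and BA with opposite sign and cancels when the sequences are balanced, so the contrast has mean 0.

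**Power, as an illustration only.** Borrow the primary outcome's ratio 20/42. Let V be the variance of a 2-week change and kV that of a 4-week change. Then Var(contrast) = (4 − k)V + 0.25τ². The last term arises because the two sequence means differ by τ. For k = 1: 3 × 1764 + 100 = 5392, SD 73.4, against a mean of 30.

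| Correlation of visits | Power at n = 37 | N for 80% |
|---|---|---|
| End-of-period comparison | 0.80 | 37 |
| Contrast, k = 1 (equal correlation) | 0.68 | 49 |
| Contrast, k = 1.5 (AR(1), ρ = 0.5) | 0.75 | 42 |
| Contrast, k = 1.75 (AR(1), ρ = 0.75) | 0.79 | 38 |
| Contrast, k = 2 (random walk) | 0.84 | 34 |

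Under AR(1), k = 1 + ρ, so the variance ratio to the end-of-period comparison is 3 − ρ (leaving out the 0.25τ² term), against a squared gain in the mean of 1.5² = 2.25. The two balance at ρ = 0.75. Simulation agrees: 0.67 with equal correlation, 0.75, 0.79 and 0.81 for ρ = 0.5, 0.75 and 0.9.

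**The case against.** The strongest defence is that the inflation is a ceiling. Whether depression and anxiety scores revert fully within two weeks of removing the blanket is unknown, and the article says that its no-residue expectation is uncorroborated. This stands: the overstatement is up to half, not half regardless. But c = 0 is the plan's own assumption, and any c below 1 leaves some inflation.

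A second defence is that the contrast cancels linear time trends, which matters in patients whose depression or medication may change. Period adjustment deals with a trend common to all patients. Patient-specific linear trends are cancelled by the planned contrast and not by a comparison of visits 3 and 4. That is a real but small cost.

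Third, a reader might infer that the contrast always loses power because it has three times the variance. The documents do not support that. A factor of three needs equally correlated visits, and no questionnaire correlation is given. With strong serial correlation the loss vanishes or reverses.

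Fourth, a reader might blame the statement that "the study will not overestimate a potential effect of PBB". That sentence concerns the missing washout, and its direction is right even here: carry-over pulls the contrast from 1.5τ towards τ. The inflation comes from the outcome definition. The sentence's conclusion nevertheless fails for these six outcomes whenever c is below 1.

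**Conclusion.** The definition is wrong as written for PSQI, HAM-D6, ISI, MDI, BAI and SCL-28. With balanced sequences and the plan's no-residue assumption, it estimates 1.5 times the true effect; in general the factor is (3 − c)/2. This is algebra on the stated visits and needs no outside figure. It rests on visit 2 being a control-condition value and on 1:1 allocation.

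The scope is limited. A reader might infer an excess of false positives or damage to the main result; neither follows. With balanced sequences the tests of no effect remain valid, and total sleep time and N = 37 are unaffected. Lower power is possible, not established: in the illustration it ranges from 0.68 to 0.84 against 0.80. A factor well above 1.5 would need a marked excess of AB patients, for which the documents give no ground.

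**What to change.** Define each questionnaire effect as the within-patient difference between the score at the end of the blanket period and the score at the end of the usual-duvet period (visits 3 and 4, assigned by sequence), adjusted for period. State the direction of subtraction, and use period rather than sequence in the HAM-D6 entry. Use visit 2 for baseline description or as a covariate, not in the contrast.

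For PSQI this also removes a mix of recall windows: the *Discussion* gives one month at visit 2 and 14 days at visits 3 and 4. With this definition the no-overestimation statement in *Statistical methods* would hold for these outcomes, since the expected value becomes (1 − c/2)τ.

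The cost is a rewording of six outcome definitions before analysis, with the same visits and the same data. The one loss is that patient-specific linear trends no longer cancel.
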